### Trial design

This prospective study investigates the impact of MAFLD on HBsAg clearance in CHB patients treated with PEG-IFN (135ug/180ug/week for 48 weeks). Patients are divided into two groups: CHB patients (*n* = 100) and CHB with MAFLD patients (*n* = 100). After treatment, participants are categorized into HBsAg clearance responders and non-responders. For HBsAg responders and HBsAg non-responders, analyzes differences in HBsAg clearance rates between CHB and CHB with MAFLD patients. Explores the impact of MAFLD on HBsAg clearance mechanisms using IHC and other methods. Compares the immunosuppressive microenvironment between responders and non-responders, focusing on T-cell characteristics. Identifies immune mechanisms contributing to HBsAg clearance. The flow chart of this study is shown in Figure 1.

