#### Secondary outcomes

A linear mixed-effects model was employed to analyze the trends in HBsAg levels over time. Random effects were included to account for inter-individual variability among patients. Fixed effects in the model included time (measured in months), group classification (e.g., responder vs. non-responder, MASLD group vs. non-MASLD group, male vs. female), and the interaction between time and group classification. Additionally, marginal effects of changes in HBsAg levels over time for different groups were estimated using generalized estimating equations (GEE). This approach provided a comprehensive assessment of the temporal variation in HBsAg levels across various patient subgroups.

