### Methods for any additional analyses

SPSS 27.0 statistical software was used for data analysis. Categorical variables were expressed as counts and percentages, while continuous variables were expressed as mean and standard deviation. Clinical data were statistically analyzed using the Kruskal-Wallis test. Variance homogeneity across groups was assessed for each test index. If the variance was homogeneous, the LSD method of one-way ANOVA was applied; if the variance was not homogeneous, the Kruskal-Wallis test was used for comparisons across multiple groups. For comparisons between the two groups, the Mann–Whitney *U* test was employed. Immunological data, including HBsAg levels, HBV DNA titers, and immune marker levels (e.g., T-cell responses, cytokine profiles), will be analyzed using appropriate statistical methods based on the data distribution. Descriptive statistics (mean, SD, median, and IQR) will be used to summarize the data. For longitudinal analysis of immune markers (such as HBsAg clearance and T-cell responses) over the course of treatment, mixed-effects models will be employed to account for repeated measures and correlations within subjects. If immunological data are not normally distributed, non-parametric tests such as the Mann-Whitney U test (for comparisons between two independent groups) or the Kruskal-Wallis test (for comparisons across more than two groups) will be used. Cox proportional hazards regression will be utilized to assess the relationship between immunological markers (e.g., HBsAg clearance, T-cell response) and clinical outcomes, such as sustained HBsAg seroclearance or progression to clinical cure. In addition, we will conduct correlation analyses (Spearman’s rank correlation) to explore potential associations between immune parameters (e.g., cytokine levels, T-cell counts) and clinical variables (e.g., liver function, ALT/AST levels). A *p*-value of <0.05 was considered statistically significant.

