### Additional consent provisions

Patients will be required to visit the hospital for assessments at baseline, Week 12, Week 24, Week 36, and Week 48 after enrollment. Routine examinations will include blood routine tests, liver function biochemistry, thyroid function, HBsAg quantification, and HBV DNA levels. Additionally, 20 mL of blood will be collected for immunological and host genetic susceptibility marker analysis.

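### HBsAg clearance, itself the outcome, is used as a term in the HBsAg-level mixed model and as a Cox predictor of clearance, so those analyses are circular

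*Protocol article*

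**What the plan says.** Trial design fixes when and how responders are defined: "After treatment, participants are categorized into HBsAg clearance responders and non-responders". Three places then use that status.

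- **Secondary outcomes (mixed model).** "A linear mixed-effects model was employed to analyze the trends in HBsAg levels over time". The fixed effects are time, "group classification (e.g., responder vs. non-responder, MASLD group vs. non-MASLD group, male vs. female", "and the interaction between time and group classification". This is the method given for HBsAg levels, so it serves the secondary outcome of quantitative HBsAg decline at 48 weeks.
- **Methods for any additional analyses (Cox model).** Cox regression is to assess the "relationship between immunological markers (e.g., HBsAg clearance, T-cell response) and clinical outcomes, such as sustained HBsAg seroclearance or progression to clinical cure".
- **Trial design (clearance rates).** "For HBsAg responders and HBsAg non-responders, analyzes differences in HBsAg clearance rates between CHB and CHB with MAFLD patients".

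The primary outcome is the 48-week clearance rate. Its analysis, under Primary outcomes, is Kaplan–Meier with a log-rank test and names no responder term. The visits listed under Additional consent provisions are "assessments at baseline, Week 12, Week 24, Week 36, and Week 48 after enrollment".

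**The concern.** Responder status is not a baseline characteristic like sex or MAFLD. It is known only at the end of treatment and is read off the HBsAg series that the mixed model describes. Responders and non-responders must lie on opposite sides of the clearance limit at that point, so a test of whether their trends differ tells the reader nothing new.

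There is a second risk if responder status and MAFLD sit in one model. Clearance is what MAFLD is supposed to influence. Holding it fixed means the MAFLD-by-time term no longer estimates the total effect of MAFLD on HBsAg decline. It estimates the difference among patients with the same end result, which is a different and usually smaller quantity.

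In the Cox analysis, predictor and outcome are nearly the same event. The Introduction and Discussion themselves treat HBsAg clearance as the marker of clinical cure.

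**Working it through.** **1. The plan's own figure, as background.** Inputs from Sample size: 35% (CHB), 60% (CHB with MAFLD), α = 0.05 (two-sided assumed), power 0.90. With unpooled variance:

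n = (1.960 + 1.282)² × (0.35 × 0.65 + 0.60 × 0.40) / 0.25² = 10.51 × 0.4675 / 0.0625 = 78.6, so 79 per group, as stated. 79 / 0.85 = 92.9, against the stated 92; 100 are planned. No sample-size figure is in dispute. The 35% and 60% are used below.

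**2. Trial design sentence, read literally.** With 100 per group at the planning rates, 35 and 60 patients clear.

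| Comparison | CHB | CHB + MAFLD | Difference |
|---|---|---|---|
| All enrolled | 35/100 = 35% | 60/100 = 60% | 25 points |
| Responders | 35/35 = 100% | 60/60 = 100% | 0 |
| Non-responders | 0/65 = 0% | 0/40 = 0% | 0 |

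**3. Cox model.** At the same rates, 65 + 40 = 105 of 200 patients never clear. None of them can have sustained clearance. If ever-cleared status is the covariate, that group has no events and the hazard ratio has no finite estimate. If clearance at an earlier visit is used, the estimate can be finite, but it still predicts the outcome from its own first occurrence. The sentence names no MAFLD term, so no MAFLD effect is lost here.

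**4. Mixed model with both terms.** Let δ be the MAFLD difference in 48-week decline without a responder term, δ* the difference with it, and γ the responder gap in decline within group. By least squares,

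δ = δ* + γ × (0.60 − 0.35).

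The loss is therefore about a quarter of γ, and γ depends on spreads that the protocol does not give. Assumptions for a simulation: mean baseline 2.2 log10 IU/mL, baseline SD 0.3 or 0.6, linear decline over weeks 0, 12, 24, 36 and 48, clearance limit 0.05 IU/mL, SD of decline 0.5 to 2.0 log10, and group means set to give 35% and 60%. Per-patient slopes were used, which is equivalent to the mixed model with balanced, complete data.

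Share of the MAFLD slope difference kept after adding responder-by-time (100,000 per group):

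| SD of decline | No floor, baseline SD 0.3 | No floor, 0.6 | Floor at limit, 0.3 | Floor at limit, 0.6 |
|---|---|---|---|---|
| 0.5 | 54% | 74% | 65% | 100% |
| 1.0 | 42% | 53% | 46% | 66% |
| 1.5 | 39% | 46% | 41% | 52% |
| 2.0 | 38% | 42% | 39% | 46% |

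Example: SD 1.0, baseline SD 0.6, no floor gives δ = 0.744 and δ* = 0.395. The ratio is 0.53, and γ is about (0.744 − 0.395) / 0.25 = 1.4 log10.

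The range kept is 38% to 100%, so 0 to 62% is removed. More than half is removed in 9 of the 16 settings.

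At the planned 100 per group (floor at the limit, baseline SD 0.6, residual SD 0.2):

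| SD of decline | Kept | Power without responder term | Power with it |
|---|---|---|---|
| 0.5 | 97% | 98% | 98% |
| 1.0 | 64% | 98% | 73% |
| 1.5 | 52% | 97% | 65% |
| 2.0 | 46% | 96% | 53% |

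**5. Mixed model, one classification at a time.** The MAFLD model then has no responder term, and 0% is removed.

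**The case against.** The best defence is that the MAFLD question is answered elsewhere. The primary log-rank comparison has no responder term, and the 2026 milestones list the difference in clearance rates separately from the comparison of cleared and non-cleared patients. That stands.

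Second, the list of classifications is given by way of example, and its wording fits one model per classification at least as well as one joint model. That also stands, and on that reading the MAFLD estimate is untouched. The responder-by-time test remains circular either way, and the text leaves open which MAFLD estimate will be reported.

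Third, the Trial design sentence is broken prose in a summary, and nobody would carry it out literally. This is fair; it calls for a clear sentence and is not evidence of a planned analysis that would fail.

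Fourth, the Cox outcome is sustained clearance or cure, which is not the identical variable, and the coding and timing of the predictor are not given. This softens the claim of an infinite hazard ratio but does not make clearance a sensible predictor of its own persistence when all patients are included.

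A reader might infer that all three analyses remove most of the MAFLD effect, or that the trial's main result is compromised. The protocol does not support that. The loss is total only in the literal Trial design reading, depends on assumptions in the mixed model, and does not arise in the Cox model.

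**Conclusion.** The plan is wrong as written on a limited point. The responder-by-time test and the Cox hazard ratio for HBsAg clearance are circular, and the Trial design sentence is empty if taken literally.

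The cost to the MAFLD estimate for the secondary outcome ranges from nothing (separate models) to about 62% (joint model), under assumed SDs of decline of 0.5 to 2.0 log10 and the other assumptions above. None of these spreads is in the protocol, so no single figure should be quoted. The primary comparison is not affected. Comparing T-cell features between cleared and non-cleared patients, a stated objective, is not circular in this sense and can stay.

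A separate, smaller matter is the word sustained in the Cox outcome. The listed visits end at week 48, so persistence cannot be seen in a patient who first clears then; those clearing at weeks 12 to 36 do have a later visit. The schedule figure was not available to check.

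**What to change.** - **Secondary outcomes:** estimate the MAFLD effect on HBsAg decline from a model with MAFLD group, time, their interaction and baseline covariates only, with no responder term. Show HBsAg trajectories by responder status descriptively, without a test.
- **Trial design:** state that clearance rates are compared between CHB and CHB with MAFLD in all enrolled patients.
- **Methods for any additional analyses:** delete HBsAg clearance from the Cox predictors. Use baseline immune markers; on-treatment markers enter only as time-varying covariates or from a landmark visit. Set the outcome to first HBsAg clearance by week 48.

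This changes analysis wording only. It needs no new data, visits or patients, and can be done before the group comparisons scheduled for 2026.

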### Methods for any additional analyses

SPSS 27.0 statistical software was used for data analysis. Categorical variables were expressed as counts and percentages, while continuous variables were expressed as mean and standard deviation. Clinical data were statistically analyzed using the Kruskal-Wallis test. Variance homogeneity across groups was assessed for each test index. If the variance was homogeneous, the LSD method of one-way ANOVA was applied; if the variance was not homogeneous, the Kruskal-Wallis test was used for comparisons across multiple groups. For comparisons between the two groups, the Mann–Whitney *U* test was employed. Immunological data, including HBsAg levels, HBV DNA titers, and immune marker levels (e.g., T-cell responses, cytokine profiles), will be analyzed using appropriate statistical methods based on the data distribution. Descriptive statistics (mean, SD, median, and IQR) will be used to summarize the data. For longitudinal analysis of immune markers (such as HBsAg clearance and T-cell responses) over the course of treatment, mixed-effects models will be employed to account for repeated measures and correlations within subjects. If immunological data are not normally distributed, non-parametric tests such as the Mann-Whitney U test (for comparisons between two independent groups) or the Kruskal-Wallis test (for comparisons across more than two groups) will be used. Cox proportional hazards regression will be utilized to assess the relationship between immunological markers (e.g., HBsAg clearance, T-cell response) and clinical outcomes, such as sustained HBsAg seroclearance or progression to clinical cure. In addition, we will conduct correlation analyses (Spearman’s rank correlation) to explore potential associations between immune parameters (e.g., cytokine levels, T-cell counts) and clinical variables (e.g., liver function, ALT/AST levels). A *p*-value of <0.05 was considered statistically significant.

### Methods used to analyze population and missing data

The missing values of all variables were adjusted by applying Multiple Imputation (MI). If more than 15 per cent of data points are missing, sensitivity analyses of the main results are conducted using multiple imputation techniques. If the missing data is determined to be not missing at random (NMAR), we will explore sensitivity analyses to assess the impact of different assumptions about the missing data mechanism. We will also provide a drop-out analysis to evaluate any potential bias introduced by participant attrition.

## Methods: monitoring

### Data monitoring committee (DMC)

This project adopts a three-tier management system involving the principal investigator, the hospital’s Research Department, and the hospital leadership. The principal investigator is responsible for the implementation and management of the project, coordinating periodic inspections and supervision conducted by the Beijing Municipal Health Commission and the hospital. Regular progress reports will be submitted to the higher-level supervisory departments and the hospital’s Research Department. Upon completion of the project, the principal investigator will assist relevant supervisory bodies in organizing the acceptance and conclusion of the project in accordance with the implementation plan.

### Interim analyses

The superior CHB cohort and the CHB combined MEFLD cohort continued to be maintained between 2025–01 and 2025–12. Regular follow-up observations were made every 12 weeks to record HBsAg and HBsAb, HBeAg and HBV DNA data and adverse events. For some of those who completed 48 weeks of antiviral therapy, the difference in efficacy between the two groups was initially analyzed.

### Adverse event reporting

All serious adverse events (SAEs) or unexpected incidents that may impact the safety or rights of study participants must be reported within 24 h of detection by the research personnel at the study institution. A comprehensive incident report must be submitted to the principal investigator and the relevant regulatory authorities. Following the report, the coordinating center will oversee the initiation of an investigation by the Ethics Committee supervising drug-related affairs to determine the cause of the adverse event. All SAEs must be thoroughly documented in the participant’s medical records or trial files. This documentation must be signed and dated by the investigator responsible for the participant to facilitate future audits and monitoring activities. Furthermore, all reported adverse events must be communicated to the Ethics Committee regularly, at intervals of 6 months, in accordance with the specific requirements of the Ethics Committee.

### Frequency and procedures for auditing trial conduct

In this study, each participating research institution will assign two independent researchers to conduct an initial review and verification of the standardized reporting format (CRF) to ensure accuracy and completeness. Following the preliminary review, a data manager will perform centralized verification to identify and correct any discrepancies or errors, with assistance from clinical monitors before the data is finalized. Additionally, a designated auditor, independent of both the investigators and the principal investigator, will conduct regular audits of the standardized reporting format at each research institution. Throughout the trial, the CRFs will undergo routine review every 6 months to ensure data integrity and compliance.

## Ethics and dissemination

### Protocol amendments and approvals

Any changes to the study protocol that may affect the study’s progress, the potential benefits to participants, or the safety of participants—such as modifications to the study objectives, design, patient demographics, sample size, procedures, or significant management details—must be formally revised. These amendments must receive approval from the Trial Steering Committee and the Ethics Committee before implementation.

Modifications proposed due to trial execution must be submitted by the principal investigator and discussed with the Multicenter Coordination Committee. These proposed amendments should be documented and signed by the principal investigator and relevant centers. The modifications can only be implemented after receiving formal approval from the Ethics Committee.

### Informed consent

In this study, we will thoroughly communicate with the patients to emphasize the importance of antiviral treatment and the significant impact of HBsAg clearance on improving patient prognosis. Informed consent will be obtained from each patient.

### Additional consent provisions

Patients will be required to visit the hospital for assessments at baseline, Week 12, Week 24, Week 36, and Week 48 after enrollment. Routine examinations will include blood routine tests, liver function biochemistry, thyroid function, HBsAg quantification, and HBV DNA levels. Additionally, 20 mL of blood will be collected for immunological and host genetic susceptibility marker analysis.

### Patient medical record confidentiality

The patient’s medical records will be kept securely and in full at the hospital where the patient receives treatment. The physician will document the results of laboratory tests and examinations in the patient’s medical records. Any public reports related to the results of this study will not disclose any personal information about the patients. We will make every effort, within the limits of the law, to protect the privacy of the patient’s personal medical information.

### Financial management of research funds

In strict accordance with the financial management regulations for research projects established by the Beijing Municipal Health Commission’s First Fund, the use of research funds will be applied for by the project leader, signed, recorded by the hospital’s research office, and approved by hospital leadership before being specifically allocated or reimbursed by the finance department. The project leader will regularly check and supervise the research progress and the usage of funds. Based on the project’s implementation, the project leader will propose adjustments to the funding and submit them for review and filing with the hospital’s finance department and research office.

### Management of adverse events and health changes during the study

If, during the study, a patient experiences any discomfort, new changes in their condition, or any unexpected events, whether related to the study or not, they must promptly notify the relevant research center physician. The physician will assess the situation and provide appropriate medical treatment. The treatment measures may include discontinuation of medication, dose reduction, or other supportive therapies. Adverse reactions during interferon therapy are considered normal; most symptoms will resolve after appropriate management. The research team will closely monitor these reactions and provide timely and appropriate interventions.

### Plan for dissemination of research findings

By the applicant’s previous research foundation and domestic and international literature, this prospective clinical study is expected to obtain a high HBsAg clearance rate, enable more patients with hepatitis B to obtain the clinical cure, greatly improve the prognosis of the patients, which can significantly reduce the transmission of HBV, reduce the incidence of cirrhosis and hepatocellular carcinoma, reduce the long-term expenditures, save more labor force, and create higher socio-economic benefits. It will provide evidence-based medical evidence for the updating of China’s chronic hepatitis B prevention and treatment guidelines. The specific research area of this topic is attributed to viral hepatitis. One of the promotion methods is to promote the experience gained in clinical and basic research of PEG-IFN treatment of advantageous CHB to colleagues in the field of hepatology through academic lectures or international and domestic academic conference exchanges. Secondly, we will publish the important experience gained from our research in the form of papers for reference by our colleagues; thirdly, we will organize a workshop on hepatitis B antiviral treatment to promote our experience.

## Discussion

The prevalence of MAFLD is steadily increasing both in the general population and among patients with CHB worldwide. Although fatty liver is recognized as a risk factor for adverse liver outcomes, including cirrhosis and hepatocellular carcinoma, its interactions with HBV and the resulting clinical effects remain complex and not fully understood.

Some studies have identified fatty liver as an unfavorable factor affecting antiviral efficacy. In a study of 213 Chinese patients with CHB treated with entecavir (ETV), the rate of HBV DNA undetectability at 24 weeks was significantly lower in patients with comorbid steatosis compared to those without hepatic steatosis (47.7% vs. 58.8%, *p* = 0.01) (18). Additionally, in a study of 89 HBeAg-positive CHB patients treated with Peg-IFN for 48 weeks, those with comorbid steatosis had significantly lower HBV DNA undetectability rates 48 weeks after discontinuation compared to those without steatosis. Multifactorial analysis showed that steatosis was an unfavorable factor for sustained viral response (OR = 0.012, *p* = 0.02) (19). The EFFORT study suggests that new-onset and persistent MAFLD in patients with HBeAg-positive CHB treated with NA may counteract the benefits of antiviral therapy, reduce the rate of ALT normalization, and negatively influence fibrosis improvement (20).

In contrast, some studies have shown that patients with hepatic steatosis are more likely to achieve HBsAg clearance. The metabolic components and immune alterations associated with MAFLD progression may directly inhibit HBV replication or indirectly induce antiviral immune responses. In patients with chronic HBV infection, comorbid MAFLD has been found to inhibit HBV replication and is associated with spontaneous HBsAg clearance (21). An international multicenter randomized controlled study of 4,769 patients with treatment-naïve CHB, treated with either entecavir (ETV) or tenofovir (TDF), with a median follow-up time of approximately 5.16 years, found that 58 patients achieved HBsAg clearance, and hepatic steatosis was identified as a favorable factor for HBsAg clearance (HR = 1.84) (22). Additionally, a previous study by our group showed that the 96-week HBsAg clearance rate was higher in inactive HBsAg carriers with moderate steatosis compared to those without steatosis (23).

In contrast, some studies have shown that steatosis is not associated with antiviral efficacy. In a retrospective study of 555 CHB patients treated with lamivudine (LAM), adefovir (ADV), entecavir (ETV), or tenofovir (TDF), multivariate analysis revealed no significant difference in HBV DNA suppression between patients with or without comorbid NAFLD (24). Another retrospective study from Taiwan involving 196 patients with HBeAg-positive CHB treated with NA monotherapy (LAM, ADV, LdT, ETV, or TDF) found that steatosis had no significant effect on HBeAg clearance (54.9% vs. 57.4%) (25).

There are differing conclusions and opinions on whether MAFLD affects antiviral efficacy. Most current studies have primarily focused on NA treatment, with therapeutic targets related to HBV DNA suppression and HBeAg conversion. However, studies on HBsAg clearance, the indicator of clinical cure, are rare. Notably, it remains unreported whether MAFLD affects the clinical cure in patients with predominantly CHB undergoing Peg-IFN treatment. This study aims to elucidate the impact of MAFLD on the clinical cure of dominant CHB patients, with the hope of guiding clinicians to more accurately screen suitable patients and promptly adjust treatment regimens.

T lymphocytes play a crucial role in the progression of HBV disease, including viral clearance, the development of hepatitis, cirrhosis, and hepatocellular carcinoma, as well as in response to antiviral therapy. CD8+ T cells are particularly important, as they can induce apoptosis in virus-infected hepatocytes. Additionally, they inhibit HBV gene expression and replication in hepatocytes through a non-cytolytic mechanism by secreting IFN-*γ*. This dual function of CD8+ T cells—mediating apoptosis and inhibiting viral replication—highlights their essential role in controlling HBV infection. When HBV infection becomes chronic, T cells gradually become dysfunctional and lose their immune efficacy as the infection progresses and antigen exposure continues. This dysfunction is characterized by a decrease in the secretion of cytotoxic factors, such as IL-2, IFN-γ, and TNF (26, 27), and an increase in the secretion of immunosuppressive factors like IL-10 and transforming growth factor-beta (TGF-*β*). Additionally, there is increased expression of inhibitory receptors such as programmed death protein 1 (PD-1), cytotoxic T-lymphocyte-associated antigen-4 (CTLA-4), and T-cell immunoglobulin and mucin structural domain-3 (Tim-3) (28, 29). Inhibitory receptors are likely the primary reason for the loss of T-lymphocyte function, leading to the body’s inability to effectively clear HBV (30). A therapeutic strategy that rescues functionally exhausted T cells by blocking inhibitory receptor signaling pathways, thereby enhancing the immune response, could integrate immunotherapy with antiviral therapy. This approach holds promise as a reliable option for patients with chronic HBV infection to achieve a functional cure.

Recent studies have reported that hepatic CD8+ T cells in MAFLD mice may play a role in alleviating hepatic inflammation and fibrosis (31). Additionally, the number of peripheral blood Th1 cells in patients with MAFLD is significantly higher than in healthy individuals, leading to the hypothesis that Th1 cells may have a pro-inflammatory role (32). However, the state of T-lymphocyte immunocompetence in patients with CHB combined with MAFLD has not yet been reported.

Based on a cohort of CHB or CHB-combined MAFLD patients receiving Peg-IFN antiviral therapy, along with a comprehensive clinical database and specimen bank, this study aims to investigate the number and function of T lymphocytes expressing inhibitory receptors in the peripheral blood of HBsAg-cleared and non-cleared patients at various time points, both at baseline and during treatment, using flow cytometry. The goal is to characterize the T-lymphocytes in patients with CHB combined with MAFLD, clarify the role of T lymphocytes expressing inhibitory receptors in HBsAg clearance, explore potential therapeutic targets, and provide insights for the development of new drugs aimed at achieving a clinical cure for hepatitis B.

Sequencing of immune cells, such as T lymphocytes and DC cells, from liver cancer patients has revealed the characteristics of immune cells within the liver cancer environment, aiding in the development of more effective immunotherapeutic targets (33). However, the application of single-cell sequencing technology in populations with CHB combined with MAFLD has not yet been explored, particularly in investigating the mechanisms involved in HBsAg clearance. In this study, we aim to use transcriptome single-cell sequencing to explore the immunomolecular mechanisms of HBsAg clearance in CHB patients with MAFLD who are receiving Peg-IFN treatment. This approach will provide a multi-stage, dynamic, and high-resolution immune landscape of the HBsAg clearance process, clarify the gene regulation of immune cells during HBsAg clearance, uncover the immune cytogenetic basis of this clearance, and identify the molecular immunogenetic markers that determine successful HBsAg clearance. In addition, although this study has adopted a prospective and multicenter study protocol to reduce sampling and follow-up bias, there are still some limitations: (1) Given that the study is multicenter and cohort-based, there may be variability in treatment outcomes due to differences in patient populations, hospital settings, and clinician practices. While we aim to include a representative sample, the findings may not be generalizable to all HBV patients, particularly those outside of the study centers or those with more advanced liver disease. (2) The study relies on patient adherence to treatment protocols, including Peg-IFN therapy, and the potential for non-compliance or early dropout could impact the results, particularly the achievement of HBsAg clearance. (3) While we will attempt to control for common confounding factors such as age, gender, and baseline liver function, there may be other unmeasured factors (e.g., genetic predispositions, lifestyle habits, or co-infections) that could influence the treatment response and the success of Peg-IFN therapy.

